#### 2.8.3 Motivation-related traits

The *Dimensions of Mastery* questionnaire (Morgan et al., 2006; Igoe et al., 2011) will be completed by parents at the baseline motor/functional assessment only. This information about the child’s underlying motivation traits may help identify personal characteristics related to engagement and learning that maybe contribute to Trexo session success.

#### 2.8.4 Individualized Trexo physical adjustment templates

Each child will have their own baseline Trexo adjustment template (Supplementary Material 3) created during their pre-physiotherapy fitting session and updated through the course of the child’s Trexo use. This template will compile Rifton Pacer settings (chest prompt size/tilt, Rifton frame height, seat height, seat angle, and seat position), Trexo leg settings (robotic leg width, knee-to-floor length, hip-to-knee length, and footplate size), and Trexo tablet settings (range of motion and optimal support forces for hip and knee joints). These settings will be selected by the treating PT to ensure good postural alignment, comfort, and adequate heel strike during walking. Since a single Trexo device will be shared across the children in the study, the research team will refer to this profile prior to each child’s physiotherapy session to make sure all child-specific physical adjustments are made to the Trexo before the session starts.

### 2.9 PT and parent perspectives

Qualitative interviews will be scheduled separately with the PT/PTA team and parents with an independent study interviewer using semi-structured interview guides. These interviews will be scheduled proximal to the pre- and post-intervention study timepoints.

Participating PTs and PTAs will have the opportunity to share their perspectives via two optional interviews: (i) reflection on the strengths and limitations of the Trexo training process used following the completion of their training and a round of Trexo physiotherapy sessions for at least one child (∼30–60 min); and (ii) Trexo user experience for each participant, following the end of that child’s physiotherapy intervention (60–90 min).

Parents’ study expectations and goals will be collected at two optional interview timepoints: (i) baseline; about Trexo outcomes goals and hopes (∼20 min); and (ii) post-Trexo intervention; focusing on observed outcomes, impressions about study methodologies, and individualized goal accomplishment including questions about overall quality of life in addition to the questions about mobility (∼45 min). Since the research team will see the child for only 2 h a week, parent feedback will be essential to capture functional changes observed in the daily living context of their child. This will also be an opportunity to solicit parental feedback on study design, tolerance, and opinions on different study aspects.

### 2.10 Adverse events

In the case of an adverse event, the study physician will be contacted for the recommended course of action, which will depend on the severity and circumstances of the adverse event. Documentation of the event will be completed by the treating PT, principal investigator, and study physician as per the study’s adverse event form. A treatment plan will be made at the discretion of the study physician. If the study team concludes that the Trexo presents a possible continuing risk to the child, Trexo treatment will be discontinued for that child and the post-Trexo outcomes assessment will be completed at that time. Additionally, the parent or child can decide to discontinue the study at any point for any reason. They will be invited to complete the next follow-up assessment at that point but are free to decline this as well. If any children drop out of the study, no children will be recruited in their place since this discontinuation of participation could point to an underlying acceptability or safety issue.

### 2.11 Data analysis

#### 2.11.1 Quantitative data analysis

*Feasibility/safety/acceptability indicators* (section “2.5 Feasibility and acceptability indicators”) will be summarized for each child’s sessions and the group descriptive statistics will be compared to *a priori* target values.

*Motor/functional assessment measures and functional priority goals* will have total/dimension scores summarized via descriptive statistics. Paired *t*-tests or non-parametric equivalents will be conducted for baseline and post-intervention time points for the co-primary measures (GMFM-88 and COPM goals), and then with each of the secondary outcomes. Correlational analyses (Pearson’s r) will also be undertaken to investigate associations between primary and secondary outcomes or with MRI results. Each clinical measure will be graphically inspected for any patterns from baseline to the optional 1-month post-intervention timepoint. For a subsample of children (undetermined subgroup ‘n’ at this point), comparisons will also be made between walking performance in the child’s regular walker and the Trexo at baseline and post-intervention.

*MRI scans* will be processed with Freesurfer Software (surfer.nmr.mgh.harvard.edu), employing a longitudinal pipeline. Automated segmentation of structural T1-weighted images will be performed, followed by quality control steps to ensure image clarity. Any neuroimaging data with excessive motion artifact will be excluded from the study. Regions of interest (ROI) will be selected based on brain areas that are most associated with gait, motor function, and motor learning. From T1 anatomical data, mean cortical thickness per brain region, and white and gray matter volumes will be calculated. Diffusion data will be used to identify and reconstruct relevant white matter tracts as well as derive DKI and DTI mean metric maps, kurtosis fractional anisotropy (FA) values, and mean kurtosis (MK), as outcome measures. From the fMRI data, ROI-specific time courses of the BOLD signal will be computed by averaging time courses across voxels within each ROI. fMRI outcome measures will include functional connectivity (FC) correlation matrices and a structural-decoupling index.

*MMG* signals will be calculated as the magnitude of the vector sum of the tri-axial ADXL335 accelerations. Data will be segmented according to periods of activity and normalized to the initial period of quiet standing for each participant. Accelerometer data will be processed using Matlab Software (Natick, Massachusetts: The MathWorks Inc.): bandpass filtered between 5 and 100 Hz (4^th^ order Butterworth filter) and processed with a symlet wavelet transform (Alves and Chau, 2010; Achmamad and Jbari, 2020). Device-induced noise will be compared in the Trexo and the child’s regular walker. Heel strike will be identified based on video recordings to demarcate phases of the gait cycle and changes in magnitude and slope of the force. We will extract and select features in time, frequency, and time-frequency domain for classification.

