**FIGURE 1 F1:**
[figure not shown]
Flow chart of study visits and timeline, reflecting O_0_ X O_1_ O_2_ design.

**TABLE 1 T1:** Research team member designations and corresponding roles in the study.

Designation	Role
Principal investigators	Responsible for study oversight and adverse event management.
Study researchers	Non-PT team members that are responsible for coordinating recruitment, scheduling, non-PT data collection, and data analysis.
Study physician	Center-affiliated pediatrician that helps with diagnostic expertise, recruitment, eligibility, and adverse event management.
Treating PTs/PTAs	Physiotherapy team members that are Trexo-trained and complete the 12 Trexo (twice weekly) intervention sessions.
PT assessors	Independent PTs (different from treating PTs) that complete the physical screening and motor/functional assessments.
Study interviewer	Independent team member that hosts all Zoom-based interviews.
MRI technician	Centre-affiliated technician that operates MRI scanner.

During ‘**O’ phases (pre/post intervention)**, participants will do their usual physiotherapy regimen (with their usual assistive device, where applicable) and associated home program, and will undergo the set of study assessments (gross motor/functional assessments and neuroimaging) in this approximately 2–3-week period pre- and post-Trexo use (Phase X). One-month post O_1_, participants will have one final motor/functional assessment and neuroimaging visit (O_2_). They will continue with their usual physiotherapy regimen during the month between O_1_ and O_2_.

**Intervention ‘X’ phase** will consist of the Trexo physiotherapy block: physiotherapy sessions twice weekly (30-min sessions excluding initial set-up time) for 6 weeks provided by a study-trained PT/Physiotherapist Assistant (PTA) team within a goal-based training program that is grounded in motor learning principles. Trexo physiotherapy will be integrated within a school-based program for half of the study cohort (*n* = 5), and within an outpatient program for the other half (*n* = 5). Each child will receive 1–2 acclimatization/fitting sessions in the Trexo before starting physiotherapy sessions. Walking tests and muscle recordings at the start and end of this phase will be done in the Trexo and in the child’s usual non-robotic wheeled walker (if they use one) for comparison and for assessment of potential carryover effects from Trexo use to their wheeled walker.

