#### 2.2.4 Sample size justification

The planned sample size of 10 children for this feasibility study will be sufficient to give an initial group picture through descriptive statistics and summary graphs of feasibility indicators and quantitative outcomes. This aligns with other quantitative pediatric therapy technology-based intervention studies that have successfully provided meaningful feasibility study results with 4 to 20 participants: (Richards et al., 1997; Wallen et al., 2008; Weightman et al., 2011; Radtka et al., 2013). This sample size will also elucidate how a single robotic assistive device may be shared (i.e., fitting adaptations to support use) among multiple children for use as a physiotherapy intervention within a center.

For the qualitative user perspective data, there is no agreed-upon sample size to achieve saturation in qualitative research (Saunders et al., 2018), instead depending collectively on sample homogeneity, interaction quality, and theoretical framework (Malterud et al., 2016).

Previous qualitative descriptive studies with children, parents, or clinicians reporting on user experiences of applying new technology or outcome measures have produced meaningful results with samples of 5 to 13 participants (Rich et al., 2014; Beveridge et al., 2015; Phelan et al., 2015; Kahlon et al., 2019; Vaughan-Graham et al., 2020; Giancolo et al., 2022; Hadj-Moussa et al., 2022; Torchia et al., 2023).

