### 2.5 Feasibility and acceptability indicators

Feasibility and safety will be quantitatively measured by a set of key process, management, and resource indicators (Tickle-Degnen, 2013; Ameis et al., 2020; Ayoub et al., 2020; Hilderley et al., 2022) with associated targets set for this study protocol. A priori targets for feasibility and acceptability are: (i) ability to enroll 80% of eligible participants that are invited to participate in the study; (ii) study retention rate of ≥ 90%; (iii) completion of awake MRIs ≥ 50%; (iv) tolerance (of setup and wear) and retention of muscle recording sensors during walking tests ≥ 75%; (v) tolerance and retention of heart rate sensor chest strap wear during gait (Trexo walker and regular walker) and motor/functional assessment ≥ 75%; (vi) tolerance of motor/functional assessments ≥ 90%; (vii) completion of parent and PT/PTA interviews ≥ 75%; (viii) adverse events “mild” severity at most and occur in ≤ 10% of physiotherapy sessions; (ix) Trexo set-up time and pauses due to adjustments significantly decrease over 12 physiotherapy session duration; (x) Trexo software or device glitches occur in ≤ 5% of sessions; (xi) motor learning strategies used “often” (25–49% of time) by PT/PTA team during physiotherapy sessions; (xii) child comfort and task enjoyment self-ratings during physiotherapy sessions reflect ≥ 80% positive scoring; (xiii) perceived study benefit by parent/clinician ≥ 80% positive scoring; and (xiv) PT/PTA training and session satisfaction ratings ≥ 80%.

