#### 2.6.1 Gross motor skills

The *Gross Motor Function Measure* (GMFM-88; Russell et al., 2000) will be administered by an independent PT assessor during the motor/functional assessment at baseline and immediately post-intervention. It will also be used 1-month post-intervention to gauge maintenance/progression of any functional gains. PT assessors will be trained on the GMFM-88 and all other PT assessment measures by the study’s co-principal investigator prior to their first study assessment. All PTs will already have extensive clinical experience administering the GMFM with children with CP, and variable experience with the other measures. The full 88-item version of the GMFM will be used as it more comprehensively captures a range of abilities in its lowest dimensions (Lie/Roll and Sit) than the abbreviated GMFM-66. This will be important as better trunk and head control are anticipated to be goals and potential outcomes associated with Trexo use in children in GMFCS Level IV. The GMFM-88 testing will be captured on video to enable post-assessment review by PTs. Pre/post change scores will be calculated with descriptive statistics representing results of the group. The GMFM has excellent test-retest reliability (Bjornson et al., 1998), and responsiveness to change (Vos-Vromans et al., 2005).

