#### 2.6.2 Functional priority goals

The PT assessor will guide the attending parent(s) through the *Canadian Occupational Performance Measure* (COPM; Law et al., 1990) during the baseline functional assessment visit to set priority outcome goals for their child. These 3–4 goals will be guided from a menu prepared by the investigators of walking-based or other functional outcomes that may arise from Trexo use. These goals can relate to the child’s abilities in home, school, or community environments. The parent(s) will use the COPM’s 10-point response scales to rate the importance of each goal, as well as satisfaction and performance of each at baseline. COPM goals will be rated by the parent(s) again at the post-intervention assessment, as well as the 1-month post intervention assessment. All efforts will be made to have the same parent attend each assessment to maintain consistency. The parent(s) and assessor will be blinded to previous COPM scores. Pre/post mean change scores will be calculated for each child. The COPM has been adapted for use with children and has demonstrated strong internal consistency, construct validity, and responsiveness to change (Cusick et al., 2007).

*Goal Attainment Scaling* (GAS) goals and achievement levels will be set by the treating PTs, and will be Trexo-directed or regular walker-associated. GAS will serve as an individualized measure of change for each child and will link to the parent-chosen COPM goals to allow evaluation of the targeted subcomponents of COPM’s higher level functional priority goals (King et al., 2000; Ostensjo et al., 2008). These two or three goals will be set by the 3*^rd^* physiotherapy session, allowing the PT team to first form a realistic idea of the child’s functional abilities and potential areas of improvement. GAS outcomes will be scored per goal by the child’s treating PT upon completion of the child’s last physiotherapy session, and a summary T-score will also be calculated. GAS is commonly used with children with CP who use walkers, and has demonstrated strong internal consistency, construct validity, and responsiveness to change (Paleg and Livingstone, 2016).

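### The 1-month GMFM-88 is meant to show whether gains last, but graphical inspection is the only analysis named for that visit; paired O2 changes with intervals should be added

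*Protocol article*

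**What the plan says.** The design in section 2.1 has three assessment phases: O0 before the Trexo block, O1 after it, and O2 one month after O1. At O2, "participants will have one final motor/functional assessment and neuroimaging visit". Usual physiotherapy continues between O1 and O2.

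The purpose of the later visit is given for the GMFM-88 in section 2.6.1: "It will also be used 1-month post-intervention to gauge maintenance/progression of any functional gains". For the COPM, section 2.6.2 says: "COPM goals will be rated by the parent(s) again at the post-intervention assessment, as well as the 1-month post intervention assessment". Table 2 also marks range of motion and Tardieu spasticity, PPAS and LSS, and PEDI-CAT at O2.

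Section 2.11.1 then assigns the analyses. Scores on the motor/functional measures and goals "will have total/dimension scores summarized via descriptive statistics", with no timepoint named. Paired t-tests or non-parametric equivalents "will be conducted for baseline and post-intervention time points for the co-primary measures (GMFM-88 and COPM goals"), and then for the secondary outcomes. For the 1-month point the text reads: "Each clinical measure will be graphically inspected for any patterns from baseline to the optional 1-month post-intervention timepoint".

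**The concern.** Whether gains last is a within-child question. It is answered by the change from O1 to O2 (was anything lost once the Trexo block ended?) and from O0 to O2 (is anything left compared with the start?). Section 2.11.1 names neither contrast. It gives the O0-O1 pair a numerical comparison and O2 a visual one, so the named method does not answer the question that section 2.6.1 sets for the visit.

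At stake is how the follow-up result will be worded. With at most 10 individual lines, whether gains were kept or faded depends on the reader's eye. A plot also does not show how large a mean loss the data still allow.

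**Working it through.** The article gives no sample-size formula, alpha, SD or effect size, so there is no figure of its own to reproduce. The check has two parts.

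**1. Do the descriptive summaries fill the gap?**

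- The summaries in section 2.11.1 may well include the O2 mean and SD.
- If the same children attend O1 and O2, the difference of the two visit means equals the mean paired change. If attendance differs, it does not.
- In neither case do the visit summaries give precision. With equal SD at both visits, the SD of the paired change is SD × sqrt(2(1 − r)), where r is the within-child correlation. Separate visit means and SDs do not contain r.
- The change scores that are named, in sections 2.6.1 and 2.6.2, are pre/post changes.

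**2. How precise would a paired O2 change be?**

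Inputs:

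- n = 10 children (section 2.2.4).
- n = 9 if the 90% retention target in section 2.5 is just met.
- n = 8 and n = 7 as assumptions for lower O2 attendance.
- Two-sided 95% intervals (assumption).

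Formula: half-width = t(0.975, n − 1) / sqrt(n), in units of the SD of the paired change.

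| Pairs | t | sqrt(n) | Half-width |
|---|---|---|---|
| 10 | 2.262 | 3.162 | 0.715 |
| 9 | 2.306 | 3.000 | 0.769 |
| 8 | 2.365 | 2.828 | 0.836 |
| 7 | 2.447 | 2.646 | 0.925 |

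If the observed mean O2-O1 change were exactly zero, the interval would still run from about −0.72 to +0.72 SD of the change with 10 pairs, and from −0.93 to +0.93 with 7.

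To express this in between-child SD units, multiply by sqrt(2(1 − r)). The documents give no r, so 0.7 to 0.95 is assumed:

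- n = 10, r = 0.7: 0.715 × sqrt(0.6) = 0.55.
- n = 10, r = 0.95: 0.715 × sqrt(0.1) = 0.23.
- n = 9: 0.60 and 0.24 for the same two values of r.

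The estimate is therefore feasible from the planned data, but imprecise.

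**The case against.** The best defence is that this is a 10-child feasibility study. Section 2.2.4 says that the sample "will be sufficient to give an initial group picture through descriptive statistics and summary graphs of feasibility indicators and quantitative outcomes", so plots of 10 trajectories fit the stated aim. The article sets no rule for calling gains maintained, and a full protocol or SAP may specify more. An interval as wide as those above could not prove maintenance either.

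Much of this stands, and it keeps the point modest. It does not remove it. The article is not silent on O2: it names a method, and a different one for O0-O1. It already plans paired tests with these children, so sample size does not explain leaving O2 unquantified. A mean change with an interval is itself a descriptive estimate. Its width is a reason to report it, because it guards against over-reading a flat line.

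A reader might infer several stronger things that the documents do not support:

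- **That fading or maintenance cannot be estimated.** It can, since the paired scores are to be collected; no estimate is named.
- **That O2 gets nothing but a graph.** The descriptive summaries have no timepoint limit and may cover O2.
- **That every O2 measure is there to test maintenance.** Section 2.6.1 says so for the GMFM-88 only. For range of motion, section 2.7.1 gives adverse-event monitoring and evaluation of change.
- **That O1 to O2 is the only Trexo-free period.** Section 2.1 describes the O0 phase as usual physiotherapy too.
- **That the paired test wastes much information from children missing O0 or O1.** This is largely hypothetical: COPM goals are set at O0, and baseline range of motion comes from screening.
- **That one mixed model is needed for every measure.** With 10 children and scales such as the LSS, which classifies sitting ability, that choice is debatable; simple paired changes suffice.

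**Conclusion.** The point holds as a mismatch between purpose and method. The 1-month GMFM-88 is there to gauge whether gains last, while the only analysis named for that visit is visual, and no O2-O1 or O2-O0 change or interval is named. No figure in the article is wrong.

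With 7 to 10 pairs the 95% half-width is about 0.93 to 0.72 SD of the paired change. That assumes two-sided 95% t-intervals and roughly normal changes. A flat-looking plot therefore does not establish maintenance, and the interval would show this where the plot would not.

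A related inconsistency affects how many pairs there will be and which children supply them. Section 2.11.1 calls the 1-month point optional, section 2.1 says that participants will have the visit, and section 2.6.3 makes only the third scan optional. If attendance is optional, the children seen at O2 may be a selected group. The documents do not show that this will happen.

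**What to change.** In section 2.11.1, keep the individual plots and add text along these lines:

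- For the GMFM-88 and COPM, the paired O2-O1 and O2-O0 mean changes will be reported with 95% confidence intervals and the number of pairs.
- The other clinical measures taken at O2 will be summarised in the same way, descriptively.
- For ordinal or skewed scales such as the LSS, the median change with a non-parametric interval will be used instead.
- These analyses are exploratory. Any statement that gains were kept or faded will rest on these estimates and intervals, not on the plot.

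Also reconcile the optional status of the 1-month visit in section 2.11.1 with section 2.1, and say whether it applies to the clinical assessment or only to the third scan.

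The cost is a few sentences and a few lines of code, with no new data. The small downside is that wide intervals become visible.

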#### 2.11.2 Qualitative data analysis

Anonymized individual physiotherapy summary profiles will be created from the session documentation, detailing goals worked on, Trexo settings used, activities undertaken, things that went well, and challenges that presented during sessions. Collective data profiles across children from their first, mid-point, and last sessions will be analyzed via a content analysis approach (settings/activities/challenges) to summarize the operational details related to Trexo use and elucidate any patterns of progression of Trexo settings, walk distances and activities undertaken within the Trexo treatment block.

*All interviews* will be transcribed within Zoom, checked afterward by the interviewer for accuracy and then de-identified prior to thematic analysis. Data will be analyzed using NVivo Software (QSR International Inc., Burlington, Canada), and an inductive content analysis approach will be taken to generate the initial codebook (Braun and Clarke, 2006). Parent and PT/PTA interviews will undergo separate thematic analysis to support within-group development of preliminary codes. Specific wording used by participants will be included in the codes to assist in preserving the meaning participants attribute to their actions and processes (Maher et al., 2018). Research team meetings will advance code-to-category-theme development and propose alternate/refined themes and interpretations until group consensus is reached.

A concurrent mixed methods approach will be taken where qualitative and quantitative data will be presented together by theme, and results reported in a narrative joint display (Fetters et al., 2013; Guetterman et al., 2015). Transferability of the results will be facilitated by reporting relevant study participant demographics to contextualize the findings.

